Written informed consent should be obtained for all eligible patients with capacity.

Written informed assent should be obtained for all eligible patients without capacity from the patient’s carer.

- - 1. **Baseline Assessments**

Baseline assessments relate to all research data collected prior to randomisation. **No protocol activity involving contact with the patients should take place before written informed consent or assent is obtained.**

Baseline data collection will be carried out at one time point whenever possible. To maximise efficiency all data will be collected during one visit. The following data will be collected;

1. Medical history
2. Functional Assessment Staging (Reisberg et al 1988)
3. Cohen Mansfield Agitation Inventory (Cohen Mansfield 1995b)
4. Neuropsychiatric Inventory (Cummings et al 1994)
5. MMSE (Folstein et al 1975)
6. Clinical Global Impression of Change scale (Guy 1976) severity at baseline and change thereafter
7. Severe Impairment Battery (Saxton et al 1990)
8. Standard side effect scale
9. Hachinksi Ischaemia index
10. List of Current Medications & Dose
11. Quality of Life in Alzheimer’s Disease Scale (QolAD) (Logsdon et al 2000)

All scales are provided at appendix 2 + 3 + 4

The research doctor or the CSO under the supervision of the PI will assess the patient, examine the medical notes/ care plans, talk to the key nurse on the ward/assisted living placement and the patients relative if possible to assist with the rating tools.

1. The researcher/CSO will ensure that the caregiver providing information has had at least 4 hours contact over the week with the patient and if possible will repeat with the same caregiver or staff with the same knowledge of the patient at later rating points.

In addition to the above, the following investigations will be performed. If recent results are available (within the last month) these will be used instead of repeating the investigation.

1. Physical examination
2. Weight
3. Blood pressure
4. ECG if clinically indicated

iv Temperature

v. blood tests: FBC, UEs, LFTs, TFTs, Glucose,B12, Folate, Cholesterol

- 1. **Randomisation & Enrolment**
     1. **Flowchart**

Consented patient with baseline assessment performed.

Allocation derived from randomisation

Treatment code allocated to patient

Treatment code corresponds to pre-randomised medication

Memantine arm

Placebo arm

- - 1. Method of Assigning Patients To Trial Arms

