**Randomisation**

Memantine group

Placebo group

2 week assessment

4+ 6 week assessment

12 week assessment

Rescue treatment as per trust protocol up to **week 3**

- - 1. **Determining Response to Memantine**

Response to memantine will be determined as follows:

- - 1. Reduction in Agitation as measured by the CMAI will be the primary outcome measure. Thus it may be expected that if Memantine is effective in treating the agitation symptoms associated with AD, then more patients will remain in the trial in the treatment group than the placebo group and there will be a reduction in Agitation score on the CMAI.
    2. Secondary outcome measures include improvement in Neuropsychiatric inventory (NPI), Clinical Global Impression (CGI), Severe Impairment Battery (SIB), Quality of Life (QOL-AD) co-prescribed medications, number of recorded incidents of aggression, and number of occasions rescue treatment utilised.

All measures will be assessed at baseline.

The following scales will be completed for each patient at 2,4, 6 and 12 weeks;

a)Cohen-Mansfield Agitation Inventory

b)Mini-Mental State Examination

c)Clinical Global Impression of Change

The NPI , SIB and QOL-AD will be measured at 6 and 12 weeks.

We will allow follow up assessments to have a 7 days window from randomisation. Baseline assessments will occur prior to randomisation and follow up assessments after randomisation.

.

- - 1. **Unblinding Reporting**

Unblinding is defined here as anyone except the randomiser who is able to identify which group (active drug or placebo) a patient has been assigned to.

If either of the above are fulfilled, a Codebreak Form should be completed **as soon as possible** after the blind has been broken by the person for whom the blind has been broken. The form should be faxed to the Chief investigator and the original kept in a locked filing cabinet.

If the codebreak is due to a Serious Adverse Event, the Serious Adverse Event Form should be completed and processed in the usual way. If the codebreak is due to a non-serious adverse event, the Adverse Event Form should be completed and filed in the source notes.

- 1. **Statistical Methods**

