6.7.5 Statistical Methods

An analysis of covariance of the post-randomisation mean CMAI scores will be carried out, with the pre-randomisation values (baseline values) used as covariate for each patient, in order to provide a comparison between the treatment groups. In this repeated measures analysis, a stationary, first order autoregressive covariance structure will be assumed for the observations in the treatment period. This analysis and its underlying assumptions are consistent with the assumptions used in the sample size calculations, to achieve 80% power. As a standard part of the statistical analysis, the underlying assumptions will be checked.

Treatment group mean comparisons with baseline values as covariates will be repeated, as secondary analyses, for assessments after 2 weeks, 4 week, 6 weeks and 12 weeks of treatment

The secondary efficacy parameters will be assessed as follows:

- the mean percent change measured on Neuropsychiatric Inventory (NPI) from baseline to endpoint after 6 weeks and 12 weeks,

- the mean percent change measured on Clinical Global Impression (CGI) from baseline to endpoint after 6 weeks and 12 weeks of treatment,
- the mean percent change measured on Severe Impairment Battery (SIB) from baseline to endpoint after 6 weeks and 12 weeks of treatment,

- the mean percent change measured on Quality of Life (QoL-AD) from baseline to endpoint after 6 weeks and 12 weeks of treatment,

These parameters will be analysed in a manner similar to that for the CMAI scores.

The difference between the Memantine and placebo group in the proportion of responders (patients achieving at least 50% reduction in their total CMAI score) will be analysed via a logistic regression model, with terms for treatment and baseline CMAI-score. Odds ratio estimates with their 95% confidence intervals will also be derived by SAS PROC GENMOD and/or PROC LOGISTIC, to measure the treatment effect.

The difference in the number of recorded incidents of aggression will be analysed with a logistic regression model containing the term for treatment only.

Demographic characteristics, clinical characteristics and co-described psychotropic medication will be summarised by frequency and percentage (discrete variables); mean, standard deviation, minimum, maximum values and 95% confidence interval for the mean (normally distributed continuous variables); median, minimum and maximum values (non- normally distributed continuous variables).

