| - ·Also used as a general term for various impressionistic measures, rated by the clinician, based on interviews with or without a collateral source, with or without reference to mental status examination, and with or without reference to cognitive assessment results - Rated on 7 points: 1 = very much improved; 2 = much improved; 3 = minimally improved; 4 = no change; 5 = minimally worse; 6 = much worse; 7 = very much worse - An overarching but implicit assumption in its use is that clinicians are sufficiently skilled to make appropriate clinical inferences and assess meaningful change in patients. Therefore, there are only minimal guidelines; there are no instructions about the kind of interview to be conducted or the method for rating change. The instructions state: "As determined by the physician relative to baseline. Rate total improvement whether or not, in your judgment, it is due entirely to drug treatment. Choose ONE response ranging from 1, very much improved ; 2, much improved; 3, minimally improved; 4, no change; 5, minimally worse; 6, much worse; 7, very much worse" |

[figure not shown]

[figure not shown]

[figure not shown]

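### The CGI is to be analysed as percent change from baseline, but its follow-up rating is already a change score and the only baseline CGI is a severity rating on a different scale

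*Protocol*

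**What the plan says.** Section 6.7.5 of the protocol defines the CGI parameter as "the mean percent change measured on Clinical Global Impression (CGI) from baseline to endpoint after 6 weeks and 12 weeks of treatment". NPI, SIB and QoL-AD get the same form of summary. The section then adds: "These parameters will be analysed in a manner similar to that for the CMAI scores". The CMAI analysis it points to is an analysis of covariance "with the pre-randomisation values (baseline values) used as covariate for each patient".

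Four other places say what the CGI is and when it is taken:

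- Section 6.3.9, Baseline Assessments, lists it as "Clinical Global Impression of Change scale (Guy 1976) severity at baseline and change thereafter".
- The section on determining response to memantine (under 6.6) names the scale for weeks 2, 4, 6 and 12 as "c)Clinical Global Impression of Change". It also says that every measure is taken at baseline.
- Appendix 3 gives the scoring: "Rated on 7 points: 1 = very much improved; 2 = much improved; 3 = minimally improved; 4 = no change", continuing to 7 for very much worse. The rater's instruction is "As determined by the physician relative to baseline".
- The visit schedule in Appendix 1 has a dash for the CGI at week 0 and crosses at weeks 2, 4, 6 and 12.

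**The concern.** A percent change needs the same quantity measured twice. NPI, SIB and QoL-AD meet that condition, since each is scheduled at baseline and at weeks 6 and 12. The CGI does not: its follow-up rating is itself the change, so no baseline value on that scale can exist. The analyst would either have no denominator or would subtract a severity rating from a change rating and divide by severity.

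At stake is a named secondary endpoint. The parameter as written gives no interpretable result, and whoever writes the SAP must either inherit it or depart from the protocol. If the choice is left until the data have been seen, the CGI analysis becomes a post-hoc selection.

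**Working it through.** The plan states no figure on this point, so there is none to reproduce. The check takes the definitions as written and computes what they give.

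**Inputs**

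- C, the follow-up change rating: 1 to 7, with 4 = no change and higher meaning worse (Appendix 3).
- S, the baseline severity rating (6.3.9). Its range is not given. I assume 1 to 7, higher meaning more severe, and show the whole range.

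**Reading A: the Appendix 1 schedule is right.** No CGI is taken at week 0. S does not exist, the percent change has no denominator, and the CMAI-type model has no CGI baseline to use as covariate.

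**Reading B: section 6.3.9 is right.** S exists, and the only percent change available is

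percent change = 100 × (C − S) / S.

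| Severity S | C = 2 (much improved) | C = 4 (no change) | C = 7 (very much worse) |
|---|---|---|---|
| 1 | +100.0% | +300.0% | +600.0% |
| 2 | 0.0% | +100.0% | +250.0% |
| 3 | −33.3% | +33.3% | +133.3% |
| 4 | −50.0% | 0.0% | +75.0% |
| 5 | −60.0% | −20.0% | +40.0% |
| 6 | −66.7% | −33.3% | +16.7% |
| 7 | −71.4% | −42.9% | 0.0% |

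For the *no change* rating: (4 − 6)/6 = −33.3%, (4 − 4)/4 = 0% and (4 − 3)/3 = +33.3%. One clinical judgement takes three values with different signs. At the extremes, a patient rated *very much worse* from severity 7 scores 0%, and one rated *much improved* from severity 1 scores +100%, which reads as deterioration.

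**What this does to the comparison between arms.** The formula equals 100 × (C/S − 1), so one step on the change scale is worth 100/S percentage points: 100/3 = 33.3 at severity 3 and 100/6 = 16.7 at severity 6. The same one-step improvement counts twice as much in the less severe patient, for no reason connected with the scale. S is measured before randomisation and so has the same expected distribution in both arms. If treatment has no effect on C, the expected difference between arms is therefore zero. The metric distorts and obscures an effect; it does not create one.

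**The case against.** Several points on the other side are fair.

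- *A baseline CGI is planned.* A reader of Appendix 1 alone might infer that no patient will have a denominator and that the result cannot be computed. The documents do not support that: section 6.3.9 and the section on determining response both provide for a baseline rating. The dash in the schedule is an inconsistency to resolve, and does not show that the rating will be missing. The mismatch of scales remains either way.
- *Randomisation protects the comparison.* A reader might infer from the table that the result would mainly reflect baseline severity. For a randomised comparison that is not shown, as the last step of the working explains. The effect estimate is oddly weighted and hard to read, but not spurious.
- *The sentence on analysing these parameters like the CMAI may name only the model.* A reader might see it as contradicting percent change. It need not: percent change can be the outcome in an analysis of covariance. For the CGI, however, it supplies no baseline on the change scale.
- *Other scales.* A reader might extend the fault to NPI, SIB and QoL-AD. These are measured on the same scale before and after, so percent change is defined except at a baseline of 0. The protocol gives no scoring range for any of the three, so whether 0 can occur is an assumption. For the NPI it is unlikely in patients enrolled for clinically significant agitation. Preferring scores is good advice here and does not correct a shown error.
- *Detail belongs to the SAP.* Section 6.7.1 promises one before the blind is broken, and the Analysis Plan section leaves the final plan to be settled with the statistician. That is a reason not to insist on one particular ordinal model. It does not excuse a stated metric that cannot work.

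**Conclusion.** The point holds for the CGI. The percent change in section 6.7.5 has no same-scale baseline. It is either undefined, if the schedule is followed, or a mixture of a severity and a change rating, if section 6.3.9 is followed. That conclusion needs no assumption; the percentages that illustrate it rest on a severity scale of 1 to 7. Separately, section 6.3.9 and the section on determining response disagree with Appendix 1 about a baseline CGI.

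The reach is limited. The CGI is one of several secondary endpoints, the change ratings will be collected as planned, and neither the primary CMAI analysis nor the sample size is touched. It should be corrected, but it does not threaten the trial's main conclusion.

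**What to change.** 1. In section 6.7.5, delete percent change for the CGI. Compare the change ratings at week 6 and week 12 directly between arms with an ordinal method, either a proportional-odds model or a rank-based test. Use baseline severity, if collected, only as a covariate.
2. Reconcile section 6.3.9 and the section on determining response with the Appendix 1 schedule, so that it is clear whether a CGI severity rating is taken at week 0. If it is, state its scoring range.
3. Optional: analyse NPI, SIB and QoL-AD as scores at weeks 6 and 12 with the baseline score as covariate. Percent change gives extra weight to patients with low baselines, and is undefined at 0 if a scale allows it.

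The cost is wording in the protocol and the SAP, settled before unblinding. No data are needed beyond the severity rating that section 6.3.9 already lists.

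### The CGI secondary endpoint is set as percent change from baseline, but the follow-up CGI is already a change rating and no baseline on the same scale exists

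*Protocol*

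**What the plan says.** Section 6.7.5 of the protocol lists the CGI among the secondary efficacy parameters as "the mean percent change measured on Clinical Global Impression (CGI) from baseline to endpoint after 6 weeks and 12 weeks of treatment". It adds: "These parameters will be analysed in a manner similar to that for the CMAI scores". The CMAI analysis described just before is an analysis of covariance with each patient's baseline value as covariate.

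Four other places determine what CGI data will exist:

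- **Section 6.6.3** names the scale completed at 2, 4, 6 and 12 weeks as "c)Clinical Global Impression of Change". It also states: "All measures will be assessed at baseline".
- **Appendix 3**, on the global impression form, gives the anchors: "Rated on 7 points: 1 = very much improved; 2 = much improved; 3 = minimally improved; 4 = no change". Scores of 5 to 7 are grades of worsening. The rating is made "As determined by the physician relative to baseline".
- **Section 6.3.9** (Baseline Assessments) lists "Clinical Global Impression of Change scale (Guy 1976) severity at baseline and change thereafter".
- **Appendix 1** (visit table) has a dash for the CGI at week 0 and a mark at weeks 2, 4, 6 and 12.

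**The concern.** A percent change needs a baseline and a follow-up value on the same scale. The protocol provides no such pair for the CGI. The follow-up score already is the change, and the only baseline value mentioned anywhere is a severity rating. No visible text schedules a severity rating at follow-up.

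This differs from the usual reservations about percent change for the NPI, SIB and QoL-AD, which all have week 0 measurements in Appendix 1. For the CGI the stated derivation does not fit the instrument. An analyst following 6.7.5 would have no denominator, or would combine two different scales, or would have to invent another derivation.

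**Working it through.** The protocol gives no effect size, SD or sample size for the CGI, so there is no figure of its own to reproduce. The check applies the stated rule under each reading of the baseline.

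**Reading A: Appendix 1, no CGI at week 0.** Percent change = 100 × (C − B)/B, where C is the follow-up rating and B the baseline value. B does not exist for any patient, so there is no denominator and no baseline covariate. The endpoint is not computable.

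**Reading B: section 6.3.9, severity S at baseline.** Percent change = 100 × (C − S)/S. The protocol does not print the severity scale; a range of 1 to 7 is assumed. All baseline severities are shown for three follow-up ratings:

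| Baseline severity S | C = 3 (minimally improved) | C = 4 (no change) | C = 5 (minimally worse) |
|---|---|---|---|
| 1 | +200% | +300% | +400% |
| 2 | +50% | +100% | +150% |
| 3 | 0% | +33% | +67% |
| 4 | −25% | 0% | +25% |
| 5 | −40% | −20% | 0% |
| 6 | −50% | −33% | −17% |
| 7 | −57% | −43% | −29% |

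Example: 100 × (4 − 6)/6 = −33% and 100 × (4 − 3)/3 = +33%, both for patients rated as unchanged. A patient rated minimally worse from severity 6 scores 100 × (5 − 6)/6 = −17%, an apparent improvement.

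Over all 49 combinations of S and C, the sign of the percentage disagrees with the rating (below 4 improved, 4 unchanged, above 4 worse) in 18, and is fully reversed in 6 of these. With S limited to 3–7 the counts are 11 of 35 and 3. Sign and rating agree throughout only when S = 4.

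**Group mean.** Take an assumed mix of S = 3, 4, 5, 6, 7 with proportions 0.10, 0.25, 0.30, 0.25, 0.10, and let every patient be rated 4. The mean is 0.10 × 33.3 + 0.25 × 0 − 0.30 × 20 − 0.25 × 33.3 − 0.10 × 42.9 = −15%. A group in which nobody changed would be reported as 15% lower.

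**Between-arm comparison.** At fixed S the percentage equals 100 × C/S − 100, which rises strictly with C. The direction of a treatment difference at a given severity is kept. Its size is not: a one-point difference in the change rating becomes 100/3 = 33 percentage points at S = 3 and 100/6 = 17 at S = 6.

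**Power.** Simulations used 66 patients per arm, the severity mix above, and a rounded normal change rating with mean 3.8, SD 1.2 and a shift of 0.5 points. All of these CGI inputs are assumptions. Across repeated runs, power was 62–65% on the raw rating and 59–61% on the percentage with severity as covariate. With no treatment effect, the percentage was rejected in 4.9% of runs by t-test and 5.4% with the covariate.

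**The case against.** A reader might infer that the endpoint simply has the wrong sign, or could reverse the treatment comparison. The documents do not support that. Only some individual scores have a misleading sign. The −15% offset is expected in both arms and cancels in a randomised contrast, direction is preserved at fixed severity, and the simulated type I error stays near 5%.

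A reader might also infer a large loss of power. Under the same assumed inputs an unadjusted t-test on the percentage reaches only about 45%. But 6.7.5 ties this endpoint to the CMAI approach, with baseline as covariate, and there the loss is a few points. Only the general mention of between-group ANOVA in the Analysis Plan section could suggest the unadjusted test.

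That the endpoint is not computable for anyone rests on one cell of Appendix 1, against two statements in the body text that point to a baseline rating. The dash may only mean that the change scale is not used at week 0. Appendix 3 is also incomplete in the copy available, so a severity form may exist. This stands as a caution, but it only moves the problem from Reading A to Reading B: 6.3.9 and 6.6.3 still specify change ratings at follow-up.

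Two further defences fail. The SAP foreseen in 6.7.1 could correct the derivation before unblinding, but only by departing from a definition the protocol itself fixes. Setting every baseline to 4 would make the percentage a simple rescaling of the rating, but nothing in the protocol says this, and a constant covariate cannot be estimated.

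**Conclusion.** Wrong as written, of moderate severity. On either reading of the baseline, section 6.7.5 gives a CGI endpoint that cannot be computed or cannot be interpreted. That conclusion comes from setting the sections side by side and needs no assumed figure. The sizes shown (−33% and +33% for unchanged patients, about −15% for an unchanged group) depend on an assumed 1–7 severity scale, and the last also on an assumed severity mix.

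The main harm is to the estimate and its reporting, not to the direction of the comparison or, under the assumed inputs, to its power once severity is a covariate. It is confined to one of several secondary endpoints. The CMAI primary analysis and the planned 164 patients are not affected, and the raw change ratings at weeks 6 and 12 are collected under every reading.

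**What to change.** In section 6.7.5, replace percent change for the CGI with a direct between-group comparison of the 1–7 change rating at weeks 6 and 12. Either a mean difference or an ordinal model would serve. Use baseline CGI severity as a covariate only if it is collected, and never subtract it from the change rating or divide by it.

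Reconcile sections 6.3.9 and 6.6.3 and the Appendix 1 visit table on whether CGI severity is rated at baseline.

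The cost is a sentence or two in 6.7.5, plus one cell in Appendix 1 or a matching wording change in 6.3.9 and 6.6.3. The change ratings are already scheduled, so no new data are needed.

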**Protocol Authorisation:**

**Chief Investigator**: **[name]: _________**

**Sponsor Representative [name] ___________________________ Date: _________**

**Trial Director-[name] ________________________________ Date: _________**

**Independent Chair-[name]: _________**

**Trial Synopsis**

| **Name of Sponsor** | East Kent Hospitals University NHS FoundationTrust |
| --- | --- |
| **Title of the Study** | A randomised, double-blind placebo-controlled trial of Memantine in the treatment of the Agitation in Alzheimer’s Dementia |
| **Trial Acronym** | MAGD – Memantine for AGitation in Dementia |
| **Investigators** | [name] (Principal Investigator); [name], [name] , [name], [name], [name], [name], [name], [name] |
| **Study Centre(s)** | Kent and Medway NHS and Social Care Partnership Trust, Oxleas NHS Foundation trust; Peterborough, Berkshire NHS Mental HealthFoundation trust, Oxford and Buckinghamshire NHS foundation trust; Plymouth |
| **Study Period** | September 2007 to May 2010 |
| **Objectives** | **Primary Objectives:** To determine the efficacy of Memantine in the treatment of acute agitation in Alzheimer’s Dementia.  **Secondary Objectives:** To estimate the overall symptom response rate to Memantine in the trial population. To investigate whether there are any adverse effects of Memantine in this population. |
| **Methodology** | A 6 week placebo controlled RCT of Memantine in AD with a blind extension to 12 weeks . Planned enrolment is 164. Patients and their clinician’s may withdraw from the study because of a clinically significant worsening in their psychiatric symptoms. These cases and those remaining under double-blind conditions will be followed for a total of 12 weeks. This will enable us to i)maximise the safety data on Memantine and ii)facilitate recruitment into the study, while retaining a strict 12 week RCT. |
| **Number of participants** | 164 |

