| **Outcome Measures** | **PRIMARY ENDPOINT**:  Change in CMAI at 6 weeks at 10mg twice daily dose – primary hypothesis 5 point difference in change score in favour of memantine. Intermediate assessment points at 2, 4, and 6 weeks.  **SECONDARY ENDPOINTS**:  Neuropsychiatric Inventory (NPI) 6+ 12 weeks, Clinical Global Impression (CGI), Severe Impairment Battery (SIB) at , 6 and 12 weeks, Change in CMAI at week 12, Quality of Life 6+ 12 weeks(QOL-AD), co-prescribed psychotropic medications, number of recorded incidents of aggression, and number of occasions rescue treatment utilised. NPI at 6 and 12 weeks  Respondent:  The difference between the memantine and the placebo groups at 6 weeks in the proportion of patients who are considered respondent. The respondent patient is a patient who had a 50% reduction in their total CMAI score. |
| **Statistical Methods** | The final analysis plan will be determined in consultation with the statistician but will involve the change in agitation inventory score from baseline to 6 weeks using the mean(SD). We may use standard survival analysis for remaining in trial and between-group ANOVA for clinical measures. |
| **Date of Final Version: 6.0 17.06.08** | |

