During the study patients will be allowed to continue taking stable doses of concomitant medicines including antidepressants, antihypertensives, anti-inflammatory drugs, atypical anti-psychotics, anticoagulants, laxatives, diuretics, hypnotics and benzodiazepines (Tariot et al, 2004). Concomitant administration of anti-parkinsonian medication will be permitted but stable dose and no patients on amantadine this is to avoid difficulties with PD stability as Memantine can have benefit in PD. Cholinesterase inhibitors will not be permitted unless patients have been stable on that medication for at least 3 months. The commencement of new psychotropic medications will not be permitted during the study except for rescue treatment as per guidelines (appendix 6) for managing the behavioural symptoms of dementia.

- - 1. **Consent / Assent**

The patient or patient’s legally authorized representative must provides written informed consent (with the patients assent) to participate in the trial

- - 1. **Subject Identification**

Patients assessed for eligibility (*prior to consent / assent for participation in the trial*) will be assigned an **identification number.**

Once randomised into the trial (*post consent / assent for participation into the trial*) a subject will be assigned a **randomisation code.**

- - 1. **Stopping Rules** There are two criteria for removal of subjects from the trial;

1. Unblinding will occur in the event of life-threatening change in physical state or need for urgent medical and/or psychiatric intervention as requested by the patient’s treating physician in consultation with the study team and study monitoring committee.

2. Drop out from the 12 week-phase of the study is permitted due to intolerable side-effects and clinically significant persistent uncontrolled agitation. This will be a primary end point but will not necessitate un-blinding for that patient.

If patients withdraw their consent for follow-up then, if at all possible, the reason for loss to follow-up should be ascertained and permission should be requested to use data collected already for the purposes of the trial. No further data will be collected on patients who withdraw from follow-up. They have the right not to give a reason for withdrawing from follow-up and also to request that no data is held on them.

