For a two-tailed test with power of 80% and statistical significance of 5% the number of patients necessary in each of two equally sized study groups is 82 (164 subjects in total) which includes a 20% attrition rate. In order to calculate the sample size, a repeated measures approach has been adopted, taking advantage of the fact that, for each patient, there will be observations at 4 different time points in the treatment period, in addition to the baseline observation. A simple covariance structure (stationary first order autoregressive) for the observations in the treatment period has been assumed (meaning that an observation for a patient at any time point is most closely associated with the immediately preceding observation for that patient). This is a weaker assumption than that of compound symmetry (the correlation between observations for a patient at different time points is the same, whatever the difference in time). Whilst this would lead to a smaller sample size, the scientific basis of the stronger assumption would be more difficult to justify.

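### The number of aggression incidents is a count, but the protocol fixes a logistic regression with treatment only, which does not suit a count and takes no account of time observed

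*Protocol*

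**What the plan says.** The Protocol's Trial Synopsis, under Outcome Measures, lists among the secondary endpoints the "number of recorded incidents of aggression, and number of occasions rescue treatment utilised". The section on determining response to memantine lists the same outcome. Neither place defines a cut-off, categories or a recording window.

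Section 6.7.5 fixes the analysis: "The difference in the number of recorded incidents of aggression will be analysed with a logistic regression model containing the term for treatment only".

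Just before that, the same section sets out the responder analysis. That outcome is binary (at least a 50% fall in total CMAI), and it "will be analysed via a logistic regression model, with terms for treatment and baseline CMAI-score".

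Four statements bear on how long patients are observed:
- Stopping Rules: "Drop out from the 12 week-phase of the study is permitted due to intolerable side-effects and clinically significant persistent uncontrolled agitation".
- Stopping Rules: "No further data will be collected on patients who withdraw from follow-up".
- Trial Synopsis, Methodology, on patients withdrawn for clinical worsening: "These cases and those remaining under double-blind conditions will be followed for a total of 12 weeks".
- Determining Response to Memantine: if the drug is effective, "more patients will remain in the trial in the treatment group than the placebo group".

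The power calculation gives 82 patients per arm, "which includes a 20% attrition rate".

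**The concern.** The question asked and the model named do not match. The question concerns how many incidents occur in each arm. Logistic regression returns an odds ratio for being in a category. To run it, someone must first turn the count into a category, and the protocol does not say how. The obvious choice is any versus none, which treats a patient with one incident like a patient with ten. In a population selected for clinically significant agitation, many patients may have at least one incident, so that split may separate the arms poorly.

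There is a second weakness. A patient observed for three weeks has less chance of a recorded incident than one observed for twelve, and a treatment-only model takes no account of this. If one arm is observed for less time, the shortfall shows up as fewer incidents.

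At stake is whether the trial can say anything useful about aggression incidents, an outcome of direct relevance to patients and carers.

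**Working it through.** The protocol states no incident rate, effect size or power for this outcome, so there is no figure to reproduce. The calculations below are illustrations.

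**Inputs from the protocol**
- 82 per arm including 20% attrition (power calculation): 82 × 0.8 = 65.6, taken as n = 65. Drop-outs are treated as contributing nothing under either model.
- Two-sided 5% level (section 6.7.1).

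**Assumptions (not in the protocol)**
- Negative binomial counts with placebo mean μ = 1, 3 or 6 incidents per patient, dispersion a = 0.5 or 1.0, and rate ratio 0.6.

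**1. Loss of information**

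Any versus none: P(at least one) = 1 − (1 + aμ)^(−1/a), with mean μ on placebo (p1) and 0.6μ on memantine (p2). Power = Φ[(|p1 − p2| − 1.96·se0)/se1], where se0 = √[2p̄(1 − p̄)/n] and se1 = √{[p1(1 − p1) + p2(1 − p2)]/n}.

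Negative binomial: SE of the log rate ratio = √{[(1/μ + a) + (1/(0.6μ) + a)]/n}. Power = Φ(|ln 0.6|/SE − 1.96).

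Worked case, μ = 3 and a = 1:
- Any/none: p1 = 1 − 1/4 = 0.750; p2 = 1 − 1/2.8 = 0.643; se0 = 0.0807; se1 = 0.0801; (0.1071 − 0.1581)/0.0801 = −0.64; power 26%.
- Negative binomial: SE = √[(1.333 + 1.556)/65] = 0.211; 0.511/0.211 − 1.96 = 0.46; power 68%.

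| Placebo mean | Dispersion | p1, p2 | Power, any/none | Power, negative binomial |
|---|---|---|---|---|
| 1 | 0.5 | 0.556, 0.408 | 39% | 58% |
| 1 | 1.0 | 0.500, 0.375 | 30% | 48% |
| 3 | 0.5 | 0.840, 0.723 | 36% | 85% |
| 3 | 1.0 | 0.750, 0.643 | 26% | 68% |
| 6 | 0.5 | 0.938, 0.872 | 24% | 93% |
| 6 | 1.0 | 0.857, 0.783 | 20% | 75% |

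The count model does better in every row, and the gap widens as incidents become more common. With greater dispersion (a = 2, means 1 to 8) both figures fall, but the order stays the same: 13–21% v 36–51%.

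**2. Unequal observation time**

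Assume equal true incident rates in both arms, a = 1, drop-outs observed for a quarter of the period, and drop-out unrelated to a patient's own incident rate. With drop-out proportion d, P(any) = (1 − d)·P(full period) + d·P(quarter period).

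At mean 1, P(full) = 0.500 and P(quarter) = 1 − 1/1.25 = 0.200. With 30% drop-out on placebo and 10% on memantine:
- Placebo: 0.7 × 0.5 + 0.3 × 0.2 = 0.41
- Memantine: 0.9 × 0.5 + 0.1 × 0.2 = 0.47
- Odds ratio: (0.47/0.53)/(0.41/0.59) = 1.28 against memantine, although the true rates are equal.

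| Drop-out, placebo v memantine | Odds ratio at mean 1 | Odds ratio at mean 4 |
|---|---|---|
| 20% v 20% | 1.00 | 1.00 |
| 25% v 15% | 1.13 | 1.17 |
| 30% v 10% | 1.28 | 1.37 |

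Each row averages the planned 20%. The split by arm and the quarter-period observation are assumptions, so the table shows how the bias could arise and not how large it will be.

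**The case against.** **The model could be ordinal.** A cumulative-logit model on grouped counts is also a logistic regression and would keep part of the information. This stands as a limit on the claim that counts are discarded, which holds for the any/none reading. It does not rescue the sentence: no grouping is given, and time observed would still be ignored.

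**The analysis plan can settle it.** The protocol says the final plan will be agreed with the statistician. But section 6.7.5 already names the outcome, the model and its only term. A plan that follows it inherits the mismatch, and one that corrects it departs from the protocol.

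**Bias against memantine is not established.** A reader might infer that the protocol expects placebo patients to leave earlier and that the result will therefore be biased. The documents do not support that. The retention statement is conditional on memantine being effective. Leaving treatment is also not the same as leaving observation, since the Trial Synopsis plans 12-week follow-up of clinical withdrawals. Only those who withdraw from follow-up give no further data. What stands is that bias is possible if retention differs by arm.

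**An unadjusted comparison is not invalid.** Leaving baseline CMAI out of a randomised comparison may cost precision, but it does not make the comparison wrong. That part is a recommendation.

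**The rescue count.** A reader might extend the same model to the number of rescue occasions. The sentence at issue does not cover that outcome. Appendix 5 limits rescue medication to the first three weeks, so total time observed would be the wrong exposure. The point does not extend to it.

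**Conclusion.** The concern holds for the mismatch between outcome and model. The outcome is a count, the fixed analysis is logistic regression with treatment only, and no step links the two. Under the any/none reading, power is roughly 20–39% where a negative binomial model would have 48–93%. These figures rest on 65 per arm, a rate ratio of 0.6, dispersion of 0.5 to 1.0 and placebo means of 1 to 6. All but the sample size and test level are assumed, so the direction is firmer than the exact figures.

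The lack of any allowance for time observed is a real but conditional weakness. It matters only if observation time differs between arms, and its size cannot be derived from the protocol.

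This is one secondary outcome. The primary CMAI analysis and the sample size are not affected. The change should be made, but the trial's main conclusion does not depend on it.

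**What to change.** Replace the sentence in section 6.7.5 with the following: the number of recorded incidents of aggression per patient, over a stated recording window, will be compared by negative binomial regression with terms for treatment and baseline CMAI and with the log of time observed in that window as offset; the rate ratio will be reported with its 95% CI. PROC GENMOD, which the section already names for the responder analysis, fits this model. The change should be made before unblinding.

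The cost is more than one sentence of text. The recording window must be defined, and each patient's observed time within it must be recorded. The visit checklist in Appendix 1 has no item for aggression incidents, so the source of the count should be stated as well.

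The offset corrects for differing observation time when leaving is unrelated to a patient's incident rate. It does not fully remove bias if patients leave because of uncontrolled agitation, and the report should say so and show observation time by arm.
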